**Figure 1 F1:**
[figure not shown]
Study design diagram. HD, health district; AICP, asthma integrated care pathway.

### Setting

2.2

The study will be carried out mainly in 2 HDs, those of Ezkerraldea-Enkarterri-Cruces and Barakaldo-Sestao, out of the 13 districts that make up our regional health service, which provides comprehensive universal health coverage, free at the point of delivery. These HDs each have a PC area and share a reference hospital. Therefore, the care pathway will be implemented in two PC areas and the PED, hospital wards, paediatric intensive care unit (PICU), and paediatric pulmonology department of their reference hospital. In the two HDs as a whole, the PC consultations deal with around 2,000 episodes of AAs per year. The reference PED deals with around 3,000 episodes of AAs per year (5% of all episodes). Selected professionals from the same levels of care in the other 11 HDs will be used as the comparison group.

### Participants

2.3

Eligibility criteria for the study will be as follows:

#### Professionals

2.3.1

All healthcare professionals providing paediatric care in Osakidetza. This includes all paediatricians and nurses caring for paediatric AAs in PC, PEDs, hospital wards, and PICUs.

#### Patients

2.3.2

All acute asthma episodes attended by any participating paediatric healthcare professionals during the study field period. An acute AA is defined as an acute episode of wheezing in a child between 2 and 14 years with a previous diagnosis of asthma or a history of wheezing; or a first episode in a child between 2 and 14 years with a personal/family history of atopy and/or an objective response to bronchodilators as assessed by the Pulmonary Score.

### Allocation to intervention and comparison groups

2.4

The paediatric professionals working in PC, the PED, hospital wards, the PICU, and the paediatric pulmonology department of Ezkerraldea-Enkarterri-Cruces and Barakaldo-Sestao HDs will constitute the intervention group and will receive the implementation strategy for the AICP. The comparison group will be made up of paediatric professionals from the other 11 HDs who will not receive any interventions. To increase comparability and reduce potential biases, two professionals from the comparison HDs will be selected for each paediatrician in the intervention group by matching in terms of paediatrician-related characteristics (e.g., baseline outcome rates, age, sex, etc.) and the characteristics of the patient population assigned to the paediatrician (size, mean age, male/female ratio, mean socioeconomic status, mean comorbidity level, etc.). This matching strategy used in the study aims to address the two main problems related to comparisons with non-randomized groups: (a) historical bias, in which events unrelated to the intervention (also referred to as secular trends) occur before or during the intervention period and have an effect on the outcome (either positive or negative) that is unrelated to the intervention; and (b) differences between intervention and control professionals, as non-equivalent control groups differ from those in the intervention in a number of significant ways that impact the outcome of interest and may bias the results (selection bias).

### Clinical intervention

2.5

The AICP is a structured multidisciplinary care plan that details the essential evidence-based steps in the care of patients with mild-to-moderate AAs and the coordinated practice of the agents involved as dictated by the evidence. In addition, the pathway determines the target population (inclusion/exclusion criteria); the sequence of common best practices during the patient's navigation through the system, according to the best available evidence in terms of: diagnostic methods and criteria, as well as their coding and recording; the provision of care and recommended clinical practices (actions, responsibilities, etc.); the educational activities for the patient and their relatives; the management of the patient and the patient's care; complex situations, management of difficulties and referral criteria; due attention to transitions between care levels and communication between professionals; and the outcomes to be pursued, evaluated and monitored.

In essence, the four core components of evidence-based clinical practice related to acute asthma as stated in the AICP (see Supplementary File S2) are:
•Assessment and recording of the Pulmonary Score;•Assessment and recording of asthma symptoms using the PACT;•Administration of background treatment in cases of persistent asthma symptoms;•Administration of bronchodilators using an MDI with a spacer chamber in children diagnosed with a mild-to-moderate asthma attack.The AICP was built on the model followed in the design of the Integrated Acute Bronchiolitis Care Pathway (29). It was developed based on the consensus of professionals involved in caring for children with asthma at different levels of care and the advice of experts in quality and medical documentation. Work started in 2020 and after an external evaluation process, its first version was approved in April 2021 (under editorial review).

### Implementation strategy

2.6

The implementation strategy to promote the adoption of the AICP is based on the one already proven effective in scaling up the Acute Bronchiolitis Pathway (29). It was also developed based on the consensus of professionals involved in caring for children with asthma at different levels of care as well as the advice of experts in quality improvement and implementation research. A Logic Model outlining how the AICP and the accompanying implementation strategy is expected to work can be found in the Supplementary File S3.

The strategy will be deployed in two implementation periods and consists of the following active components (see Supplementary File S1):
(1)First implementation period:
•Initial dissemination of the AICP document and support materials through several web seminars (using the ZOOM platform) for professionals within the organizations involved•Integration of information and communication tools into electronic health records (EHRs) to facilitate the recording and the standardized implementation of recommended practice actions, including access to educational material to be provided to patients and families•Delivery of training courses for paediatricians and paediatric nurses•Distribution of monthly audit/feedback reports with data on changes in the AICP indicators at their health centre level and those obtained in other centres in the participating health areas•Circulation of newsletter notifications with AICP-related messages.(2)Second implementation period (in addition to the previous strategies):
•Multi-channel dissemination of the AICP to professionals through various communication and training actions: General presentations to professionals within organizations involved through several web seminars (ZOOM sessions); dissemination and review of the active components and innovative aspects of the AICP via videos available through the intranet and online; weekly training “pills” through corporate social networks on epidemiological data and data regarding the health, economic and social impact of the AICP; key messages on current treatment recommendations based on the latest CPGs and the recommended protocol; and reminder posters distributed to all paediatric services, the PED and hospital outpatient clinics.•Dissemination to healthcare users: reminder posters distributed to all paediatric services, the PED, and hospital outpatient clinics with QR codes for accessing educational content (e.g., videos).

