### Evaluating the effectiveness of the AICP

2.8

The main effectiveness outcome will be the change from baseline to 12 and 24 months in the rates of mild-to-moderate AA episodes seen in PC and the PED in which patients are administered bronchodilators using a MDI with a spacer chamber. We will assess the overall effect of the AICP by testing the interaction between intervention and time of measurement. Should this intervention-by-time interaction be significant (with *p* < 0.05 as the threshold for significance), planned comparisons will be performed to determine whether changes in the AICP group between baseline and each of the follow-up points are significantly different from those observed in the control group. Secondary effectiveness outcomes will be the change from baseline to 12 and 24 months after the implementation of the AICP in: (a) rate of recording of Pulmonary Score at all levels of care; (b) rate of recording of asthma symptoms using the PACT at all levels of care; and lastly, (c) the change in rate of persistent asthma symptoms in children who initiate a background treatment at all levels of care.

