### Data management plan

2.10

This study will be carried out in accordance with international standards for the conduct of epidemiological studies, included in the International Guidelines for Ethical Review of Epidemiological Studies (37). In order to learn about the management of AAs, data will be collected from the health centres and the PED and inpatient care-paediatric pulmonology reference centres of the two HDs. This is a prospective intervention study, where the data will be collected from the EHR, using the data exploitation program of our regional health service (OSABIDE Global). The Primary Care Research Unit of Bizkaia is formally authorized by the Healthcare Directorate of Osakidetza to extract and use data from the EHR for research purposes. A diagnostic search will be carried out for the term asthma with AAs (International Classification of Diseases code J45.901). Data will also be gathered on the number of prescriptions given for inhaled bronchodilators, or inhaled and systemic corticosteroids, the recording of severity using the Pulmonary Score, and the use of a spacer chamber in mild-to-moderate attacks. In the case of prescriptions, only those made using the Basque Health Service prescription platform and associated with AA episodes will be recorded. As this data collection and recording will be performed without naming and without any participation of the patients as it is mainly routine clinical practice data, need for consent was waived by the ethics committee. Conversely, participants in the structured focus group meetings (both professionals and patients’ relatives/caregivers) will be informed about the study and their written informed consent will be obtained concerning the information directly collected from them (see Supplementary Files S5, S6).

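### The primary outcome is read from a record that the intervention itself is meant to improve, so a positive result shows more recorded spacer use but not necessarily more actual spacer use

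*Protocol article*

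**What the plan says.** **What the intervention arm receives.** Among the first-period components, section 2.6 lists: "Integration of information and communication tools into electronic health records (EHRs) to facilitate the recording and the standardized implementation of recommended practice actions". It also lists: "Distribution of monthly audit/feedback reports with data on changes in the AICP indicators at their health centre level". Second-period strategies are added to these, so both continue.

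**Which practices are covered.** Section 2.5 names four core components. One is: "Administration of bronchodilators using an MDI with a spacer chamber in children diagnosed with a mild-to-moderate asthma attack".

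**What the comparison arm receives.** Section 2.4 describes the comparison professionals as those "who will not receive any interventions".

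**What is claimed.** Section 2.8 defines the main effectiveness outcome as the change in the rate of mild-to-moderate episodes "in which patients are administered bronchodilators using a MDI with a spacer chamber". Section 2.11 uses the same idea of administration.

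**How it is measured.** Section 2.10 states that "the data will be collected from the EHR, using the data exploitation program of our regional health service". Among the items gathered it lists "the recording of severity using the Pulmonary Score, and the use of a spacer chamber in mild-to-moderate attacks". The article describes no other source for spacer use.

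**The concern.** The same record serves as a target of the intervention and as the measuring instrument for the primary outcome. The professionals who write the record are the ones who receive the tools and the feedback. As described, these reach one arm only, after a baseline year that precedes the first implementation period.

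For the Pulmonary Score and the PACT this does no harm, because recording is what those outcomes are about. For the primary outcome the claim concerns treatment given. A clinician who used a spacer before and after, but documented it more often after, would count as improved.

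The likely direction favours the pathway, and the Discussion says the results will inform scaling up to the whole regional service. At stake is whether a positive result can be read as a change in care or only as a change in recorded care.

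**Working it through.** **1. The plan's own figure.** Section 2.11 gives 1,100 primary care episodes per year in the two intervention districts, 10% v 15%, a two-sided 5% chi-square test, 20 episodes per professional and 80% power. It states no intracluster correlation (ICC), so the power can only be solved backwards.

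- Without clustering and with equal groups, n per arm = [1.96·√(2·0.125·0.875) + 0.842·√(0.10·0.90 + 0.15·0.85)]² / 0.05² = 686.
- Implied design effect = 1,100/686 = 1.60, so ICC = (1.60 − 1)/(20 − 1) = 0.032.
- With two comparison episodes per intervention episode, the need is 502 in the intervention arm. The design effect is 1,100/502 = 2.19 and the ICC is 1.19/19 = 0.063.

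The 80% is attainable under an unstated but plausible ICC. The point here does not depend on it.

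**2. What the analysis can identify.** Let π be true spacer use and c the share of true use that is recorded, and assume no false recording. Then recorded rate = π × c. If completeness is constant in the comparison arm:

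recorded rate ratio = true rate ratio × (c after / c before)

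Only the product is observed. The planned ratio of 15/10 = 1.5 could be 1.5 × 1.0 (all care), 1.2 × 1.25 (mixed) or 1.0 × 1.5 (all recording). The interaction term takes the same value in each case.

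**3. Illustration with no change in care.** I take the plan's 10% as a recorded rate. The values of true use and completeness are assumptions; none is in the documents.

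| True use, both arms | Completeness before | Completeness after, intervention arm only | Recorded before → after |
|---|---|---|---|
| 20% | 50% | 75% | 10% → 15% |
| 30% | 33.3% | 50% | 10% → 15% |
| 50% | 20% | 30% | 10% → 15% |

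Odds ratio = (0.15/0.85)/(0.10/0.90) = 1.59.

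There is a limit. Completeness cannot exceed 100%, so recording alone gives the whole contrast only if true use is at least 15% and baseline completeness is at most 10/15 = 67%. Smaller gains give less: true use of 20% with completeness rising from 50% to 60% gives 12% recorded, an odds ratio of 1.23.

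**4. Chance of a significant result from recording alone**, using the plan's simple two-sample test, 1,100 intervention episodes and design effect 1 + 19 × ICC:

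| ICC | 10% → 15%, 1:1 | 10% → 15%, 2:1 |
|---|---|---|
| 0.032 | 80% | 90% |
| 0.05 | 72% | 84% |
| 0.10 | 55% | 69% |

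For the smaller gain (10% → 12%) at ICC 0.032, the chances are 22% (1:1) and 29% (2:1). These are not results for the planned mixed model.

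**5. What the safeguards cover.** Section 2.4 says matching is aimed at secular trends and at differences between the groups. Section 2.11 adds propensity scores, baseline adjustment and random effects. Matching on baseline rates equalises recorded rates before the tools arrive. None of these acts on a change in recording that the intervention itself causes. The Discussion names generalisability as the limitation and does not mention documentation.

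**The case against.** The case on the other side has real content.

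- **The spacer field is an inference.** A reader might infer that a new structured field for spacer use was installed. Section 2.6 speaks of recommended practice actions in general. In section 2.5 the spacer component is worded as administration, whereas the Pulmonary Score and PACT components are worded as assessment and recording. The link to spacer use runs through its place among the four core practices and no further. This limits the point but does not remove it: monthly feedback on the indicators is also an incentive to document.
- **Visibility in the comparison districts is not stated.** A reader might infer that those districts certainly lack the tools. The extraction program belongs to the regional service, and the article does not say where the change is visible. Section 2.4 says those professionals receive no interventions. If the tools are visible there, the feedback would still be one-sided.
- **Some of any rise may be real care.** The same component also aims at standardised practice, and the Introduction cites pathways that increased use of recommended medication. The documents do not support calling a positive result an artefact.
- **No simple check settles it.** It is tempting to read parallel rises in any-bronchodilator use and spacer use as proof of a recording gain. Real care could produce both. Conversely, suppose any bronchodilator is charted in 60% of episodes throughout (an assumption) and only spacer documentation rises from 10% to 15%. The share by spacer then goes from 0.10/0.60 = 17% to 0.15/0.60 = 25% through documentation alone. Prescriptions do not help either: section 2.10 describes collection in the two intervention districts, and a prescription does not show how a drug was delivered during a visit.
- **This is an implementation trial.** Recording tools are part of the package, and reach and adoption are openly defined by registered practice. That is legitimate for those outcomes. It does not make the effectiveness outcome, worded as administration, a measure of administration.

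**Conclusion.** The concern holds as a limit on interpretation. As the article describes the design, an intervention that promotes recording is delivered to one arm, and an outcome phrased as treatment given is read from that record. The planned interaction test cannot tell more spacer use from more complete documentation, and no stated safeguard addresses the difference.

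The size of the bias cannot be computed from the documents. Under assumed completeness, a 1.5-fold rise in one arm would reproduce the full planned contrast with no change in care. That shows what is possible, not what is likely. The conclusion rests on the comparison arm not receiving the tools or the feedback, as section 2.4 states, and on spacer use being among the practices whose recording is promoted.

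**What to change.** 1. **Wording (sections 2.8, 2.11 and 3).** Define and report the primary outcome as recorded administration by MDI with spacer. Name differential documentation between arms as a limitation on any claim that care changed.
2. **Extraction (section 2.10).** Apply the same definition of the numerator to both arms and all periods. State whether the electronic tools are visible in the comparison districts.
3. **Supportive analyses, pre-specified, by arm and period.** Report the rate of any recorded bronchodilator administration, and the share by MDI with spacer among those episodes. Add a sensitivity analysis that uses only record sources available in the baseline year.

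These analyses should inform the interpretation. They should not be a condition for the primary claim or proof either way. The baseline-source analysis should not replace the primary one, because it can discard genuine administrations documented only in newer sources.

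**Cost.** Changes of wording and a few further analyses on the same extract, with no new recruitment. The conditional share has a smaller denominator and is less precise, and the baseline-source analysis may understate a true effect.

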### Outcome measures

2.7

The impact evaluation of the AICP implementation will be conducted using the Reach, Effectiveness, Adoption, Implementation, and Maintenance (RE-AIM) framework, an evaluation framework developed by Glasgow et al. (32) to extend the assessment of interventions beyond effectiveness or efficacy to multiple criteria that can better identify the public health impact of health promotion programmes, initiatives or interventions.

### Evaluating the effectiveness of the AICP

2.8

The main effectiveness outcome will be the change from baseline to 12 and 24 months in the rates of mild-to-moderate AA episodes seen in PC and the PED in which patients are administered bronchodilators using a MDI with a spacer chamber. We will assess the overall effect of the AICP by testing the interaction between intervention and time of measurement. Should this intervention-by-time interaction be significant (with *p* < 0.05 as the threshold for significance), planned comparisons will be performed to determine whether changes in the AICP group between baseline and each of the follow-up points are significantly different from those observed in the control group. Secondary effectiveness outcomes will be the change from baseline to 12 and 24 months after the implementation of the AICP in: (a) rate of recording of Pulmonary Score at all levels of care; (b) rate of recording of asthma symptoms using the PACT at all levels of care; and lastly, (c) the change in rate of persistent asthma symptoms in children who initiate a background treatment at all levels of care.

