### Effectiveness objectives

1.1

To evaluate the effectiveness of the implementation of the AICP on: (a) increasing the rate of administration of bronchodilators using a metered-dose inhaler (MDI) with a spacer chamber in children diagnosed with a mild-to-moderate AAs in PC, PEDs, and hospital wards; (b) increasing the Pulmonary Score documentation rate at all levels of care; (c) increasing the rate of recording asthma symptoms using the Pediatric Asthma Control Tool (PACT) (31) in PC and PEDs; and (d) increasing the rate of initiation of background treatment in children with persistent asthma symptoms, in PC and PEDs.

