### Analysis

2.11

Frequencies and proportions along with the corresponding 95% confidence intervals (CIs) will be used to describe the rate of administration of bronchodilators using an MDI with a spacer chamber in paediatric asthma patients at all measurement points. The primary effectiveness outcome will be the changes in this bronchodilator use rate in children diagnosed with mild-to-moderate AAs in primary care, the PED, and hospital wards. To test the overall effect of the AICP, we will compare changes in outcome variables between the two groups over the three follow-up measurements adjusted for baseline values. Given the binary nature of most response variables (prescription rates or performing certain clinical practices/actions), the underlying regression model will be a logistic regression model, and hence, odds ratios or risk ratios will be calculated as estimators of the effect of the intervention. Multivariate mixed logistic models will be used to take into account the hierarchical structure of the data, with patients nested in paediatricians and/or health centres in each of the measurement periods (SAS PROC GLIMMIX ver. 9.4, SAS Institute, Cary, NC, USA, 2023). Separate models will be fitted for data from PC centres and EDs due to differences in the hierarchical structure of the data. In both PC and ED-related models, the AICP intervention, the time of measurement and intervention-by-time interaction will be included as fixed effects. Paediatricians and centres will be included as random effects in the intercept and the slope of the different repeated measurements in PC models, while a structure of patients nested in hospitals will be fitted for ED data, as patient care at EDs cannot be assigned to any specific physician. In all mixed models fitted, restricted maximum likelihood ratio tests and the Akaike and Bayesian information criteria will be used to estimate the modelled parameters (fixed and random), and to determine the best covariance structure for our data, respectively. Backward selection of effects with *p* < 0.05 as a threshold for inclusion and Laplace approximation will be used to identify parsimonious final multivariate mixed logistic models.

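### The primary rate counts only mild-to-moderate episodes, yet the only severity variable named is the Pulmonary Score, whose recording the pathway promotes in one arm, so the denominator may shift by arm

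*Protocol article*

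**What the plan says.** All references are to the protocol article.

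- **Outcome.** Section 2.8 (Evaluating the effectiveness of the AICP) defines the primary outcome over "the rates of mild-to-moderate AA episodes seen in PC and the PED". Section 2.11 (Analysis) describes it as "changes in this bronchodilator use rate in children diagnosed with mild-to-moderate AAs in primary care, the PED, and hospital wards".
- **Finding episodes.** Section 2.10 (Data management plan): "A diagnostic search will be carried out for the term asthma with AAs (International Classification of Diseases code J45.901". No severity grade is attached to the code.
- **Severity.** The same section lists, among the data to be gathered, "the recording of severity using the Pulmonary Score, and the use of a spacer chamber in mild-to-moderate attacks". No other severity variable is named.
- **Recording as a target.** Section 1.1 has the objective of "increasing the Pulmonary Score documentation rate at all levels of care". Section 2.5 lists "Assessment and recording of the Pulmonary Score" as a core component, and section 2.8 makes the "rate of recording of Pulmonary Score at all levels of care" a secondary outcome. Section 2.6 supports recording with tools in the electronic record, training and monthly audit and feedback.
- **Comparison arm.** Section 2.4 says that the comparison professionals receive no intervention.
- **Power.** Section 2.11 uses 1,100 acute asthma episodes a year in primary care, with no restriction by severity or recorded score.

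**The concern.** The effect is read from the intervention-by-time interaction, so it is a comparison of changes between arms. That comparison is sound only if the same kind of episode is counted before and after in each arm. Here the variable that appears to decide whether an episode counts is one that the intervention is designed to make more complete.

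Matching on baseline characteristics does not help, because the shift arises after baseline. The interaction test does not help either, because recording is pushed up in one arm only. A change in which episodes are counted could hide a real change in spacer use or imitate one.

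**Working it through.** **Inputs from the article.** Reference rate 10%, target rate 15%, 1,100 primary care episodes a year, 20 episodes per professional, two-sided 5%, power 80% (all section 2.11).

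**Assumed inputs.** The article gives no recording rates, no severity shares and no link between scoring and spacer use. I assume that recording rises from 20% to 60% in the intervention arm, that it does not change in the comparison arm, and that true spacer use in mild-to-moderate episodes stays at 10%. Any measured change is then an artefact.

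**1. The plan's own figure.** With equal arms and no clustering, 10% against 15% needs 686 episodes per arm for 80% power. With 1,100 per arm, 80% power implies a design effect of 1100/686 = 1.60. The intraclass correlation is then (1.60 − 1)/19 ≈ 0.032. The article does not state this correlation, so the 80% can be neither confirmed nor refuted. What matters here is that it rests on all episodes. The planned odds ratio is (0.15/0.85)/(0.10/0.90) = 1.59.

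**2. Only scored episodes count.** Let spacer use in already-scored episodes be *k* times that in unscored ones.
- Unscored rate: *b* = 0.10/(0.2*k* + 0.8)
- Measured baseline rate: *a* = *kb*
- Measured follow-up rate: (0.2*a* + 0.4*b*)/0.6

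| *k* | *b* | Baseline | Follow-up | Change (points) | Spurious OR |
|---|---|---|---|---|---|
| 1 | 10.0% | 10.0% | 10.0% | 0 | 1.00 |
| 1.5 | 9.1% | 13.6% | 10.6% | −3.0 | 0.75 |
| 2 | 8.3% | 16.7% | 11.1% | −5.6 | 0.63 |
| 3 | 7.1% | 21.4% | 11.9% | −9.5 | 0.50 |

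The sign can reverse. Suppose scoring is unrelated to spacer use at baseline, but at follow-up 80% or 90% of spacer episodes are scored against 60% overall. The measured rate then goes from 10% to 0.10 × 0.8/0.6 = 13.3%, or to 0.10 × 0.9/0.6 = 15.0%, with no true change.

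**3. Unscored episodes count as mild-to-moderate.** Let a share *v* of episodes be severe with no spacer use, leaving the denominator only when scored. With a share *s* recorded, the measured rate is 0.10(1 − *v*)/(1 − *vs*).

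| *v* | *s* = 20% | *s* = 60% | Spurious OR |
|---|---|---|---|
| 10% | 9.2% | 9.6% | 1.05 |
| 20% | 8.3% | 9.1% | 1.10 |
| 30% | 7.4% | 8.5% | 1.16 |

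Under either handling, the denominator depends on recording.

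**The case against.** The strongest reply is that the article never says severity is derived from recorded scores. Its wording about children diagnosed with mild-to-moderate attacks could mean the clinician's judgement, and a condensed article may leave the coding rule to the full protocol. The power statement, which uses all episodes, even suggests that the working denominator may not be restricted at all. This stands in part: score-only classification is an inference. But the article fixes a severity-restricted outcome and names one severity variable, and that combination is enough to put the primary estimate at risk.

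A reader might go further in several ways that the documents do not support:

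- **Unscored episodes are certainly dropped.** No rule for them is given.
- **Some first episodes qualify only if scored.** Section 2.3.2 offers "an objective response to bronchodilators as assessed by the Pulmonary Score" as one route, but a history of atopy alone suffices, and extraction is by diagnostic code.
- **The comparison denominator stays fixed.** Section 2.4 itself anticipates secular trends. All that can be said is that recording is not promoted there. If it rises there too, the difference between arms is smaller than illustrated.
- **The artefact is very large.** Spacer use of 30% in scored and 5% in unscored episodes would give a fall of about 17 points, from 30% to (0.2 × 0.30 + 0.4 × 0.05)/0.6 = 13.3%. No figure in the article supports a six-fold gap.
- **The background-treatment outcome has the same flaw.** Section 1.1 speaks of treatment started in children with persistent symptoms, while section 2.8 words the outcome the other way round. The argument does not carry over as it stands.

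**Conclusion.** The concern holds in conditional form. Unless severity comes from a source independent of the recorded Pulmonary Score, the primary denominator depends on something the intervention changes in one arm, and neither the matching nor the interaction test removes the resulting bias.

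The direction is not determined, and the bias is nil if scoring is unrelated to spacer use and severity. Under the assumed rise in recording, the artefact is a fall of about 3 to 9.5 points if only scored episodes count (*k* = 1.5 to 3). It is an odds ratio of about 1.05 to 1.16 if unscored episodes count as mild-to-moderate (10% to 30% severe). For scale, the planned effect is 5 points, or an odds ratio of 1.59. The point falls are measured from inflated baselines of 13.6% to 21.4%, so the odds ratios are the fairer comparison.

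**What to change.** - Analyse spacer use over all coded acute asthma episodes at ages 2 to 14, whether or not a score was recorded. Make this the primary analysis, or at minimum a pre-specified sensitivity analysis that must agree before an effect is claimed.
- Make no exclusion based on a recorded score. Removing only episodes recorded as severe recreates the dependence shown in step 3 of the working.
- Keep the mild-to-moderate rate alongside it.
- State where severity comes from and how unscored episodes are classified.
- Report score-recording rates by arm and period.

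The extraction is the same, so the cost is wording. The downside is dilution, because the pathway specifies the practice for mild-to-moderate attacks and some severe ones would be counted. For example, if 15% of episodes were severe with no spacer use, and the 10% and 15% rates apply to mild-to-moderate episodes, the contrast becomes 8.5% against 12.75%. With 686 effective episodes per arm, power would be about 72%. If 686 counts only the mild-to-moderate episodes, the total is 686/0.85 = 807 and power is about 79%. If those rates already refer to all episodes, as the wording of the power statement suggests, the stated 80% is unaffected.
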